### Study design and setting

The comparative cohort study will be in keeping with a quantitative, descriptive and longitudinal 12-month design of adult patients presenting with FEP that are either HIV infected or non-infected. The study will take place in the eThekwini District, one of 11 in KZN Province, with an estimated population of 3 442 361 people. The district has a high HIV burden, with an estimated 650 000 people living with the virus in 2018.^34^ In addition, there are only five hospitals in the municipality with psychiatric services managed by a psychiatrist, at which the study will be conducted. The hospitals selected are the four general hospitals with specialist psychiatric services situated in eThekwini: Addington, King Edward VIII, Prince Mshiyeni and RK Khan Hospitals, and at King Dinuzulu Hospital, which serves as the psychiatric hospital for the area. All hospitals have inpatient and outpatient psychiatric services and receive referrals from within the district as well as from urban and rural areas as far south as the Eastern Cape Province and northern KZN.

### Eligibility criteria

#### Inclusion criteria

Male and female patients will be included if they are inpatients or outpatients, aged 18–45 years, have a first presentation to mental healthcare services for FEP meeting Diagnostic and Statistical Manual (DSM)-V criteria^35^ (American Psychiatric Association (APA) 2013) for a psychotic disorder, are neuroleptic naive or minimally treated (maximum 6 weeks of psychotropic treatment in this first episode), and provide consent to participate.

#### Exclusion criteria

Patients will be excluded if they have been prescribed antipsychotics in the past or have had previous psychotic episode, an intellectual disability (assessed clinically or by chart review) or other significant general medical conditions that may be associated with FEP, for example, epilepsy or syphilis, have less than 7 years of formal schooling and refuse consent.

### Participant selection and sampling strategy

All adult inpatients or outpatients with FEP meeting the inclusion criteria will be recruited to the study over a 3-year period. The sample size calculation was based on a log-rank test group. In order to achieve an 80% power to detect an OR of 1.857 (to maximise variability), in a design with three repeated measurements having a compound symmetry covariance structure when the proportion from group 2 is 0.500, the correlation between observations on the same subject is 0.500, and the alpha (significance) level 0.05 or 5%, a sample of 130 PLWHIV and FEP and 130 HIV negative with FEP will be required. In addition, this sample size accounts for and permits a 10% dropout rate over an anticipated 36-month accrual with a minimum follow-up of 12 months.

### Data collection

The study will use a clinical interview, physical examination, several psychiatric tools and HIV-related haematological tests to measure variables. Baseline measures will be done within 6 weeks of first presentation and as soon as the participant is able to consent. Participants need to have responded to antipsychotic medication and will be assessed to have the capacity to consent by a treating and research doctor. The study (HIV+) and control groups (HIV−) will receive the same baseline assessments and follow-up at 3, 6 and 12 months, which are summarised in table 1. The HIV-negative group will have HIV testing at each visit to re-confirm HIV status. The study procedures, with instruments,^36–46^ that will be used are shown in the information in figure 1. Data will be collected manually and captured electronically.

Clinical researchers with a medical background will administer the mental health diagnostic assessment, the MINI 7.02, Psychotic Disorders version, DSM-V^36^ and diagnostic interview face-to-face, and will be supported by a trained research assistant who will facilitate the self-report questionnaires. All study personnel will be trained on initiation of the study with an annual refresher training on the different tools by psychiatrists with research and clinical experience. A medical doctor will conduct the clinical assessments, collect the biological specimens (table 1), and conduct the HIV counselling and testing. We will use an HIV COBAS COMBI test to detect both HIV antibodies and p24 antigen. Standard pre-test and post-test counselling will be delivered in a culturally sensitive manner, while the CD4 count and viral loads will be measured at every visit among PLWHIV.

Participants will be given a return research appointment date and telephonic contact will be maintained between interviews. The study team (research assistant and clinician) will contact participants to remind them of appointments to limit their withdrawing from the study. For participants who do not arrive for their appointments, the research assistant will contact the patient to reschedule an appointment in the same week.

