**Methods and analysis:**

This study will compare presentation, course, and outcome of a cohort of PLWHIV and FEP with a control group recruited over a 3-year period. We will prospectively test the hypothesis that the 2 groups are socio-demographically, clinically and cognitively distinct at illness presentation, with higher trauma burden and poorer outcomes in those with the dual burden of HIV and FEP. FEP participants, confirmed by a structured neuropsychiatric interview, will have their socio-demographic, psychosis, mood, motor, trauma and substance use variables assessed. A neuropsychological battery will be completed to assess cognition, while quality of life, psychotic symptoms and HIV markers will be measured at 3, 6 and 12 months.

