## Methods

Patients referred to the participating psychiatry units will be screened by the respective treating doctors for eligibility for recruitment into the study. The patients with FEP must fulfil the inclusion criteria and will be referred to the designated investigator at each unit. Once written informed consent has been obtained, the protocol for data capture will be followed, as per the list outlined in figure 1 and table 1, the same protocol being followed for outpatients and inpatients. The clinical examination and psychiatric tests, which take approximately 2 hours, will be undertaken by the investigators who are all medical practitioners. Patient baseline assessments will be undertaken within 6 weeks of treatment during their outpatient visit or following admission to the respective units at baseline. A physical examination, body mass index and waist circumference measure will also be obtained by a medical practitioner. Where possible, collateral information from a next of kin, with the participant’s consent, will also be sought. The follow-up visits will be done at 3, 6 and 12 months as outpatients, and the participants will be reimbursed for travel costs. Attempts will be made to coincide each of these with scheduled clinic follow-up visits and will be performed by the same initial interviewer at each psychiatry outpatient department.

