### Ethics and dissemination

Ethical approval to conduct the study was obtained from the Biomedical Research Ethics Committee of the University of KwaZulu-Natal (UKZN). The study will be conducted in accordance with South African Department of Health Research Ethics guidelines (2015) as well as the UKZN policy on Research Ethics. Recruitment of study participants will commence as full ethics approval was received from Biomedical Research Ethics Committee. No other independent ethics review was required.

All participants fulfilling the inclusion criteria will be selected for the study, from whom written, informed consent will be obtained. All potential participants will have the opportunity to participate, which will be made known to them in the information sheet. Where participants are unable to consent independently, adequate steps will be taken to ensure that legally acceptable proxy consent is obtained. All participants testing HIV positive at any point in the study will be referred for ART and support.

The results from this investigation will be actively disseminated through peer-reviewed journal publications and conference presentations. On completion of the peer-review process, we will provide feedback to clinicians at Department of Health for further discussion about enhanced treatment algorithm.

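### Data collection makes response to antipsychotics an entry condition that the eligibility criteria lack, so baseline symptom scores need not describe illness presentation

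*Protocol article*

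**What the plan says.** All places are in the protocol article.

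- **Data collection:** "Participants need to have responded to antipsychotic medication and will be assessed to have the capacity to consent". The same paragraph counts six weeks from first presentation and waits until the participant can consent.
- **Inclusion criteria:** patients qualify if they "are neuroleptic naive or minimally treated (maximum 6 weeks of psychotropic treatment in this first episode), and provide consent to participate". Response is not mentioned.
- **Exclusion criteria:** "Patients will be excluded if they have been prescribed antipsychotics in the past or have had previous psychotic episode". Non-response is not listed.
- **Participant selection and sampling strategy:** every adult with first episode psychosis who meets the inclusion criteria is to be recruited over three years, with 130 per group.
- **Ethics and dissemination:** "Where participants are unable to consent independently, adequate steps will be taken to ensure that legally acceptable proxy consent is obtained".
- **Methods, opening paragraph:** "Patient baseline assessments will be undertaken within 6 weeks of treatment". Table 1 places visit 1 in the first six weeks without saying from what.
- **Abstract and Aims:** the hypothesis is that "the 2 groups are socio-demographically, clinically and cognitively distinct at illness presentation", and the Aims compare presentation, course and 12-month outcomes by HIV status.

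**The concern.** Who enters the cohort depends on which section a site follows. A patient treated for a few weeks without response is eligible under three sections and barred by a fourth. A patient without capacity is admitted by proxy in one section and shut out in another. Five hospitals recruit, so different sites could apply different rules.

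Two comparisons are exposed. The first is the baseline comparison, which is claimed for illness presentation but would rest on scores taken after treatment had worked. The second is the 12-month comparison, where poorer outcomes are expected with HIV. Early response is plausibly related to outcome, so selecting on it may remove more poor-outcome patients from one group than from the other. Data management and analysis names t-tests and chi-squared tests for group comparisons, which do not address this. The limitations section mentions hospital-based sampling and unstandardised treatment, but not selection on response.

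**Working it through.** **Step 1. Apply each rule to the same patient.**

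| Patient | Inclusion, exclusion and sampling sections | Data collection | Ethics and dissemination |
|---|---|---|---|
| Treated up to 6 weeks, responded, has capacity | in | in | in |
| Treated up to 6 weeks, no response, has capacity | in | out | no response rule |
| Lacks capacity throughout the window | in, if proxy consent counts as consent | out | in, by proxy |
| Naive on arrival, then treated, responded, has capacity | in | in | in |
| Still naive at consent | in | cannot qualify | no response rule |

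Rows 2 and 3 conflict on the plain wording. Row 5 conflicts only if naive describes status at consent. If it describes status on arrival, row 4 applies and nothing clashes.

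**Step 2. Compare the clocks.** Methods counts six weeks from treatment, and Data collection counts them from first presentation. The two agree when treatment starts at presentation. They separate when treatment in this episode began earlier, which the inclusion criterion permits.

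**Step 3. See what baseline measures.** Table 1 first measures PANSS, PHQ9, ESRS and the cognitive screens (CAT-Rapid, IHDS) at visit 1. Under the response condition these are on-treatment scores. Socio-demographic data, duration of untreated psychosis and the CTQ do not change with weeks of treatment, so they are exposed only through who is selected. The full cognitive battery is scheduled at 3 and 12 months, so it is not a presentation measure under any reading.

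**Step 4. Find when the HIV contrast is biased.** Let q be the fraction of a group left out for non-response, and d the mean outcome of non-responders minus that of responders.

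- Full mean = (1 − q) × responder mean + q × non-responder mean, so responder mean = full mean − q × d.
- Contrast among responders = full contrast − (q₁d₁ − q₀d₀), where 1 is HIV-positive and 0 is HIV-negative.

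With equal d, the shift is zero when q is equal and grows with the difference in q. For on-treatment scores, the observed gap equals the gap at presentation minus the between-group difference in improvement up to the rating. Time to response can therefore matter even with equal q.

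**Step 5. Illustrate the scale.** The documents give neither q nor d. Assume d = 1 SD in both groups and a difference in q of 5 to 15 percentage points. The shift is 0.05 × 1 to 0.15 × 1 = 0.05 to 0.15 SD. If HIV-positive patients respond less often, it runs towards no difference. With 130 per group, the standard error of a mean difference is √(2/130) = 0.124 SD, and the difference detectable with 80% power is 2.80 × 0.124 = 0.35 SD. The assumed shift would be 0.05/0.35 = 14% to 0.15/0.35 = 43% of that. This is an illustration, not an estimate.

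**Step 6. Set aside the sample size.** An odds ratio of 1.857 against 0.50 gives 0.65. With maximum variance, two-sided 5% and the compound-symmetry factor (1 + 2 × 0.5)/3 = 0.667, the calculation gives 116.3, rounded up to 117. Then 117/0.9 = 130, so the stated figure reproduces and is not in dispute. It counts enrolled patients only. If 50% to 90% of eligible patients responded in time (assumed), 130 enrolled would need 130/0.5 = 260 down to 130/0.9 = 145 eligible per group.

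**The case against.** The strongest defence reads the sections as a sequence: the patient arrives untreated, is treated, regains capacity, consents and is rated. The response sentence sits between two statements about ability to consent and gives no definition or threshold. It may mean only that the patient is settled enough to consent. On this reading there is no naive-versus-responder contradiction, and the two clocks largely coincide.

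Much of this stands. A reader might infer that admitting neuroleptic-naive patients flatly contradicts the response condition. The text does not establish that, because it does not say when naivety is judged. A reader might also infer that baseline spans 0 to 6 weeks of treatment, but a responder cannot have had zero. It is also fair that much of the baseline comparison (demographics, untreated duration, childhood trauma) does not change with weeks of treatment.

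The sequence reading does not resolve the rest. It leaves assessed capacity against proxy consent, and it leaves a response requirement stated in words that the eligibility sections lack. It also concedes that symptom scores are taken on treatment. Because capacity itself may depend on improvement, entry on capacity alone could still select to some degree.

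A screening log and covariate choices are often left to a full protocol. The finding here is the conflict in the stated text, and those items are part of the remedy.

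**Conclusion.** The point holds as a conflict in the stated entry and consent rules, with a consequence for what baseline can show. Response and capacity are required in one section, absent from the eligibility criteria and, for capacity, overridden by proxy consent in another. Applied as written, the Data collection rule yields PANSS, PHQ9, ESRS and cognitive-screen scores that are on-treatment values in early responders, not values at presentation.

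Bias in the HIV contrast is conditional: it needs response, time to response or the non-responders' deficit to differ by HIV status. A reader might infer a bias of known size or direction, or that the whole presentation comparison fails. The documents support neither. They give no response rate and no difference by HIV status, and several baseline variables are exposed only through selection. The range of 0.05 to 0.15 SD rests entirely on assumed inputs.

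**What to change.** 1. Reconcile Methods, Inclusion criteria, Exclusion criteria, Participant selection and sampling strategy, Data collection, and Ethics and dissemination into one entry and consent rule. It should say whether response is a condition, how proxy consent fits with assessed capacity, and at what moment naive status is judged.
2. Use one starting point for the six-week baseline window.
3. If the response condition stays, define the population as early responders and describe baseline symptom scores as on-treatment severity. Align the Abstract and Aims with that.
4. Record days on antipsychotic at the baseline rating, and log eligible patients not enrolled by HIV status and reason. If not recorded during accrual, this information may be unrecoverable.
5. Report treatment days by group. Treat any adjustment for them as a sensitivity analysis only, because HIV status and recovery may both influence them and adjustment could remove or distort part of the HIV effect.

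The cost is protocol wording, one extra baseline field, a screening log and a narrower claim about presentation. No extra procedures are needed.

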**Figure 1 F1:**
[figure not shown]
List of all study procedures used in the patient assessment.

**Table 1 T1:** Objectives and measures used at each visit in HIV-infected and non-infected participants

Domain	Measures	Source of measures/tool	Visit 1	Visits 2 and 3	Visit 4
			Within first 6 weeks	At 3 and 6 months	At 12 months
Demographic factors	Socio-demographic data	Socio-demographic questionnaire	X		
Mental health outcome (objective 1)	Psychosis	Psychiatric history and MINI	X		
	DUP and pathways to care	WHO Encounter	X		
	Severity and nature of psychosis symptoms	PANSS	X	X	X
	Depression	PHQ9	X	X	X
	Trauma	CTQ	X		
		PCL		X	
	PTSD	Clinician-administered PTSD scale for DSM-V (CAPS 5)		X	
	Motor symptoms	ESRS	X	X	X
	HIV-associated cognitive deficit screen	CAT-Rapid and IHDS	X	X	X
	Social cognition	Neuropsychological battery		X (at 3 months only)	X
	Substance use	WHO ASSIST	X	X	X
	Quality of life	WHO-QOL BREF	X	X	X
	Biochemical haematological and radiological tests	From hospital records: full blood count, liver function test, syphilis and hepatitis test. Cerebrospinal fluid biochemistry and neuroimaging if available			
Clinical markers of HIV (objective 2)	HIV status	Confirmatory HIV ELISA			
	HIV marker	VL if HIV positive	If applicable	If applicable	If applicable
	HIV marker	CD4 if HIV positive	X		

ASSIST, Alcohol, Smoking and Substance Involvement Screening Test; CAPS, Clinician-Administered PTSD Scale; CAT, Cognitive Assessment Tool; CD, cluster of differentiation; CTQ, Childhood Trauma Questionnaire; DUP, Duration of untreated psychosis; ESRS, Extrpyramidal Symptom Rating Scale; IHDS, International HIV Dementia Scale; MINI, Mini International Neuropsychiatric Interview; PANSS, Positive and Negative Syndrome Scale; PCL, Psttraumatic Stress Disorder Checklist; PHQ, Patient Health Questionnaire; PTSD, Posttraumatic Stress Disorder; QOL BREF, Quality of Life; VL, viral load.

The cognitive battery assessment, which takes approximately 2 hours, will be administered by a clinical psychologist, at the 3-month and 12-month visits. Translation services will also be available for patients who require isiZulu translation during the interviews.

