Following collating the data for steps 1–13 in figure 1 and table 2,^22–33^ we will perform steps 14 and 15 after voluntary counselling and testing. The required HIV tests, CD4 count and viral load if HIV positive, as per the protocol, will be taken by a medical practitioner at each site. HIV testing will be carried out at baseline for all participants as well as at each visit for HIV-negative participants. A patient with a positive HIV test will be referred to the HIV clinic at the site for further management. Other investigations, such as lipid profile, which are part of routine care, will be captured from the clinical records.

**Table 2 T2:** Cognitive test battery and domains to be tested

Domains	Test
Motor skills	Grip strength^22^, Pegboard^23^
Visuospatial functioning	WAIS-R Block Design, Digit symbol^24^, and Rey-Osterrieth Rey Complex Figure (RCF)—Copy^25^
Verbal memory	Rey Auditory Verbal Learning Test (RAVLT)^26^
Non-verbal memory	RCF—Recall^25^
Problem solving/reasoning	WAIS-R Language test^24^
Language	RAVLT^26^
Word generation	Controlled Word Association Test (COWAT)^27^ Animal Naming (Letter and Category cues)^28^
Attention	WAIS-R Digit Span^24^
Executive functioning	Trail making^29^, RCF^25^, Wisconsin Card Sorting Test (WCST)^30^
Social cognition	Emotion perception (Faces Test)^31^, Theory of mind (Eyes Test)^32^, Social knowledge (Situational Feature Recognition Test) (SFRT)^33^

COWAT, Controlled Word Association Test; RAVLT, Rey Auditory Verbal Learning Test; RCF, Rey-Osterrieth Rey Complex Figure; SFRT, Situational Feature Recognition Test; WAIS, Wechsler Adult Intelligence Scale; WCST, Wisconsin Card Sorting Test.

We are keen to explore impact of pathways of care on socio-demographic and clinical variables. Rehabilitation programmes are limited as many sites lack a multidisciplinary team to support this; however, standard of care includes medication, supportive therapy, psycho-education, referral to psychology if indicated and management of comorbid substance use.

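### Clinician-rated scales at follow-up are likely to be scored with knowledge of HIV status, because rating and HIV testing fall to the same role and the same interviewer returns at each visit

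*Protocol article*

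**What the plan says.** The Data collection section assigns three tasks to one role: "A medical doctor will conduct the clinical assessments, collect the biological specimens (table 1), and conduct the HIV counselling and testing". The Methods section says that the clinical examination and psychiatric tests are "undertaken by the investigators who are all medical practitioners", and that the follow-up visits "will be performed by the same initial interviewer at each psychiatry outpatient department".

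The HIV procedures differ by group at each visit. For those without HIV, "The HIV-negative group will have HIV testing at each visit to re-confirm HIV status". For those with HIV, "the CD4 count and viral loads will be measured at every visit among PLWHIV". Table 1 marks CD4 at Visit 1 only, but allows viral load at all visits, so the groups differ on either reading. Under Study progress and challenges, participants who seroconvert stay in follow-up and the change of status is noted.

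At baseline, Methods (the paragraph between Tables 1 and 2) has steps 1 to 13 collated first: "we will perform steps 14 and 15 after voluntary counselling and testing". The cognitive battery at 3 and 12 months "will be administered by a clinical psychologist". Self-report questionnaires are facilitated by a research assistant.

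The Abstract states the expected direction: the groups differ at presentation, "with higher trauma burden and poorer outcomes in those with the dual burden of HIV and FEP". The limitations in the summary box and under Methodological challenges cover hospital-based sampling, tool validity, language and non-standardised treatment. They do not mention rating with known HIV status.

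**The concern.** PANSS, ESRS and CAPS-5 depend on the judgement of the person scoring them. If that person knows the HIV status and shares the stated expectation, a small unconscious shift in scoring would differ between the groups being compared. The planned t-tests and chi-square tests would read the shift as a difference between groups. Adjustment for confounders would not remove it, because it sits in the measurement and moves with the exposure itself. It has to be handled when the data are collected.

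**Working it through.** **1. Who rates, and what the rater knows**

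| Point | What the article fixes | Consequence |
|---|---|---|
| Ratings and HIV testing | Same role, a medical doctor (Data collection) | The role that scores also handles the result |
| Follow-up | Same interviewer as at baseline (Methods) | Knowledge gained at or after baseline carries forward |
| Tests at visits | Retesting in one group, viral load in the other (Data collection, Table 1) | Visit procedures reveal the group |
| Baseline order | Testing after steps 1 to 13 (Methods) | A new diagnosis may be unknown at the first rating; a status already known is not masked |
| Cognitive battery | Clinical psychologist at 3 and 12 months (Methods) | A separate assessor; awareness of status not stated |

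I take the clinician-rated scales to be among steps 1 to 13 of Figure 1.

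**2. Which ratings are exposed**

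Table 1 schedules PANSS and ESRS at all four visits, so three of the four ratings come after the baseline test. CAPS-5 is marked only under Visits 2 and 3, that is at 3 and 6 months. PHQ9 and WHO-QOL BREF depend less on the rater.

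**3. Where 117 per group comes from**

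The article plans 130 per group and allows 10% dropout: 130 × 0.90 = 117. As a check on 130:

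- OR 1.857 against a proportion of 0.50 gives 1.857 / 2.857 = 0.65.
- Log-odds-ratio formula, two-sided 5%, 80% power: n = (1.960 + 0.842)² × [1/(0.65 × 0.35) + 1/(0.50 × 0.50)] / (ln 1.857)² = 172.0.
- Three measurements with correlation 0.5: factor (1 + 2 × 0.5)/3 = 2/3, giving 114.7.
- Dropout: 114.7 / 0.90 = 127.4, so 128, close to the stated 130.

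The point does not rest on this figure, and masking raters would not change it.

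**4. Illustration of sensitivity**

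Assume no true difference and a constant rating shift of d standard deviations against the HIV group. The values of d are assumptions and are not in the documents. With a two-sided 5% normal test and n = 117 per group:

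- Non-centrality at one visit: λ = d × √(117/2) = d × 7.649.
- Rejection rate = Φ(λ − 1.96) + Φ(−λ − 1.96).
- For the mean of three visits with correlation 0.5, λ is divided by √(2/3).

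| Assumed shift d | λ, one visit | p < 0.05, one visit | p < 0.05, mean of three visits |
|---|---|---|---|
| 0 | 0 | 5% | 5% |
| 0.1 SD | 0.765 | 11.9% | 15.5% |
| 0.2 SD | 1.530 | 33.4% | 46.6% |

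Averaging over visits makes this worse: it reduces random error and leaves a constant shift in place.

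**The case against.** The case on the other side has real force.

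- **A role is not a person.** A reader might infer that one named doctor gives each participant the HIV result and then scores that participant. The article does not say so. It separately has clinical researchers give the diagnostic interview and a medical practitioner at each site take the HIV bloods. This stands, and is why the point says likely. But nothing in the article separates the two tasks, and Methods refers to a designated investigator at each unit.
- **These are not declared the main outcomes.** A reader might treat PANSS, ESRS and CAPS-5 as the primary measures. The article ranks no outcome, and the Abstract names quality of life and HIV markers beside psychotic symptoms. The point is therefore confined to the clinician-rated scales.
- **Baseline is handled.** Partly: the order of testing protects new diagnoses only.
- **Known exposure is an ordinary constraint of a cohort, and a constant interviewer limits between-rater variation.** Both are fair. Neither prevents the constant interviewer from being someone other than the tester.
- **The psychologist may already be unaware of HIV status.** Possibly. The article is silent, and such detail may sit in a fuller protocol, so this is an available safeguard and no demonstrated fault.
- **The shifts are hypothetical.** Correct. They show sensitivity and do not estimate bias.

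**Conclusion.** The point holds in a limited form. Followed as written, the article makes it likely that PANSS and ESRS at 3, 6 and 12 months, and CAPS-5 at 3 and 6 months, are rated with knowledge of the comparison variable, under a directional hypothesis and without this being listed as a limitation.

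This rests on the plain reading that the shared role means shared knowledge of the result, and on the same-interviewer rule being kept. The 12% to 33% false-positive range at one visit applies only under the assumed shifts of 0.1 to 0.2 SD.

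A reader might go further and conclude that the results will be biased towards the hypothesis. The documents do not support that: neither the size nor the direction of any bias can be derived from them. The change is still worth making, because it is cheap and the problem cannot be repaired in the analysis.

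**What to change.** Use existing staff:

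1. Keep HIV status out of the clinical psychologist's referral and test file for the 3- and 12-month battery.
2. Where a site has two investigators, split the work from baseline. One does the ratings at all visits, which keeps the same-interviewer rule; the other does the HIV counselling, testing, CD4 and viral load.
3. At each rating, record whether the rater knew the HIV status. Use this in a sensitivity analysis, for example the group difference among ratings made without that knowledge. Awareness will not arise at random, so treat the result as supportive only.
4. Where separation is not possible, list unmasked rating as a limitation.

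Putting the ratings before the HIV tests within a follow-up visit would do little alone, because a returning interviewer who also tests already knows the status. The CAPS-5 schedule need not change.

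The cost is some scheduling effort and one form field; the sample size stays at 130 per group. Masking will sometimes fail, because participants disclose their status or records show it. At single-investigator sites only the psychologist can be masked.
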